### Progression Criteria

The prespecified criteria for advancing to an effectiveness trial are as follows: reach of 60% or more; retention of 70% or more; mean Bot Usability Scale, Acceptability of Intervention Measure, and Intervention Appropriateness Measure scores above 4; mean distrust score below 4; mean trust score above 4; and 70% or more of the participants completing the chat session and T1. Effectiveness measures (DSES and GHSQ) are exploratory, intended to inform the design of any future effectiveness trial, and are not progression metrics. If the criteria are not met, qualitative findings will be used to determine whether barriers are modifiable at the design level or structural, distinguishing between tool adaptation and revision of the implementation strategy as the appropriate response.

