#### Proposed Approach

We propose a nonrandomized feasibility pilot that deploys the community-informed SARHAchat prototype on 2 social media platforms identified by the target population (ages of 18‐25 years; HRSA-designated rural NC and SC counties) during phases 1 and 2. This “meet people where they are” implementation strategy departs from traditional clinic-based digital health delivery and tests a potentially more equitable and scalable approach to reaching rural young adults.

A total of 75 pregnancy-capable individuals aged 18 to 25 years residing in HRSA-designated rural counties will be recruited via social media geofencing, accounting for a projected 20% attrition rate and yielding a target of 60 completers, which is consistent with published recommendations for digital health feasibility studies [27]. To achieve this within a 16-week recruitment window, the required enrollment rate is approximately 4.7 participants per week. Prospective monitoring will trigger adaptive recruitment if fewer than 30 participants have been enrolled by week 8.

Eligible participants will complete an electronic informed consent form and a baseline survey (T0; digital health literacy, decision self-efficacy, and demographics), immediately engage with the enhanced SARHAchat prototype to complete one pathway (eg, contraception consultation or question-and-answer session) with a guided prompt or their own questions, and then complete a postinteraction survey (T1; usability, acceptability, appropriateness, trust, and decision self-efficacy). A purposively selected subsample of 20 participants will complete semistructured interviews to provide explanatory qualitative depth (Figure 2).

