
**Table 1. T1:** Proposed feasibility outcomes, instruments, time points, and prespecified progression thresholds for aim 2, organized within the reach, effectiveness, adoption, implementation, and maintenance (RE-AIM) framework.

RE-AIM domain	Outcome and measure	Time point	Prespecified threshold
Reach	Enrollment rate and consent rate	16-wk recruitment window	≥60% of target (n≥45 enrolled)
Effectiveness	DSES^a^ [35] and adapted GHSQ^b^ [36]	DSES: T0^c^ and T1^d^; GHSQ: T1	Exploratory; no progression threshold; mean T0-T1 DSES change and T1 GHSQ
Adoption or engagement	Proportion completing the chatbot pathway among all enrolled	After interaction	70% or more of the participants completing a session
Implementation—usability	BUS-11^e^ [32]	T1	Mean BUS-11>4
Implementation—acceptability	AIM^f^ [33]	T1	Mean AIM>4
Implementation—appropriateness and trust	IAM^g^ [33] and TPA^h^ [34]	T1	Mean IAM>3; mean distrust<4; mean trust>4
Implementation—retention	Proportion completing the T1 survey after completing the chatbot pathway	T1	70% or more of the participants completing a session
Maintenance	Tool uptime (percentage of time that the chatbot is accessible) and reported error or failure rates	After T1	≥80% uptime and ≤20% error or failure rate

a DSES: Decision Self-Efficacy Scale.

b GHSQ: General Help Seeking Questionnaire.

c T0: baseline.

d T1: after interaction with the chatbot.

e BUS-11: Bot Usability Scale.

f AIM: Acceptability of Intervention Measure.

g IAM: Intervention Appropriateness Measure.

h TPA: Trust Between People and Automation scale.

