### Data Integrity, Missing Data, and Handling of Incomplete or Failed Interactions

A participant is classified as a completer only when the Qualtrics (Qualtrics International Inc) T0 submission, the back-end pathway-complete event, and the Qualtrics T1 submission all exist for the same study ID (Figure 2). All thresholds are calculated against the number enrolled except for retention, which is calculated among pathway completers to isolate postengagement attrition. Geographic eligibility will be verified by comparing self-reported county with the IP address captured by the Qualtrics screener; discordant or anonymized (eg, virtual private network) locations will be manually reviewed and screened out if unresolved via a brief verification contact. Duplicate enrollment and potential bot submissions will be addressed through Qualtrics duplicate submission and bot controls. Only the first consented record will be retained. IP addresses will remain in the siloed screening dataset, used solely for eligibility verification and duplicate detection, and will be deleted when recruitment closes.

Participants without a pathway-complete event within 2 days of T0 will be counted as noncompleters for the adoption threshold, and their partial engagement (number of exchanges and last conversational stage reached) will be described to identify points of disengagement. Back-end logs will distinguish verified technical failures (system unavailability, response generation errors, and loss of session state) from user abandonment and from safety guardrail activations, which reflect intended behavior and are reported separately. Technical failures contribute to the maintenance error rate (≤20%), and affected participants may reattempt using their original study ID, with adoption status determined via eventual pathway completion. Participants whose session is interrupted by a technical failure may resume via their original study ID within 7 days; sessions not completed within this window are classified as noncompleters. Given the pilot’s descriptive scope, analyses will follow an available-case approach. Scale scores will be computed when at least 80% of items are answered, DSES change will be limited to participants who complete both T0 and T1, and baseline characteristics of completers and noncompleters will be compared descriptively.

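### The completion criterion for progression is stated in two incompatible ways: about 49% of those enrolled under Table 1, 70% under Progression Criteria

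*Protocol article*

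**What the plan says.** Three parts of the Protocol article bear on completion.

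- **Table 1** (Data Analytical Plan, phase 3), whose title describes its thresholds as prespecified for progression. Adoption is measured as "Proportion completing the chatbot pathway among all enrolled" and retention as "Proportion completing the T1 survey after completing the chatbot pathway". Both rows carry the same threshold text: "70% or more of the participants completing a session".
- **Data Integrity, Missing Data, and Handling of Incomplete or Failed Interactions.** The denominator rule is: "All thresholds are calculated against the number enrolled except for retention, which is calculated among pathway completers". The same section defines a completer jointly: T0, the pathway-complete event and T1 must all exist for one study ID.
- **Progression Criteria.** This section has no separate adoption item. It lists retention of at least 70% and then, as a further item, "70% or more of the participants completing the chat session and T1".

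For scale, phase 3 plans to enroll 75, "accounting for a projected 20% attrition rate and yielding a target of 60 completers", and reach passes at "≥60% of target (n≥45 enrolled").

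**The concern.** Table 1 puts a 70% floor under each of two successive steps. Progression Criteria puts a 70% floor under the two steps taken together. These are different rules, and both are presented as the prespecified basis for the decision to advance.

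The wording of the retention row adds to the difficulty. Its measure is T1 completion after the pathway, but its threshold speaks of completing a session, as the adoption row does. Read literally, Table 1 sets no threshold for T1 at all.

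At stake is the completion part of the go/no-go decision. If completion comes in between the two floors, the verdict depends on which section is read, and whoever settles that will already have seen the data.

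**Working it through.** **Inputs.** 75 enrolled, 20% attrition and 60 completers (Phase 3, Proposed Approach); reach floor of 45 enrolled, adoption 70% and retention 70% (Table 1); enrolled denominator for everything except retention (Data Integrity section); joint 70% (Progression Criteria).

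**The plan's own figures reproduce.** 60 / (1 - 0.20) = 75, and 45 / 75 = 60%.

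**Floors implied by each rule.** Under Table 1, full completion / enrolled = adoption x retention, so the floor is 0.70 x 0.70 = 0.49. Under Progression Criteria it is 0.70. In whole participants:

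| Enrolled | Pathway completers needed (Table 1) | T1 needed (Table 1) | Full completers needed (Progression Criteria) |
|---|---|---|---|
| 75 | 0.70 x 75 = 52.5, so 53 | 0.70 x 53 = 37.1, so 38 (50.7% of 75) | 53 (70.7%) |
| 45 | 0.70 x 45 = 31.5, so 32 | 0.70 x 32 = 22.4, so 23 (51.1% of 45) | 32 (71.1%) |

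**One data set, two verdicts.** Take 75 enrolled, 53 pathway completers and 38 T1 surveys.

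- Adoption: 53 / 75 = 70.7%, met.
- Retention: 38 / 53 = 71.7%, met. Table 1 passes.
- Joint completion: 38 / 75 = 50.7%, not met. Progression Criteria fails.

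With exactly 53 pathway completers, every result from 38 to 52 full completers splits this way (23 to 31 at 45 enrolled). With more pathway completers the range narrows: at 60 of 75, retention needs 0.70 x 60 = 42, so the split runs from 42 to 52.

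**Redundancy within Progression Criteria.** Let F be full completers, P pathway completers and N enrolled, with F ≤ P ≤ N. If F / N ≥ 0.70, then P / N ≥ F / N ≥ 0.70 and F / P ≥ F / N ≥ 0.70. The joint criterion already guarantees retention and adoption, so the separately listed retention item can never decide anything.

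**How often the two rules would disagree.** These are exact binomial sums at 75 enrolled. The stage rates are assumptions, not figures from the protocol.

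| Assumed adoption / retention | Joint rate | Table 1 passes | Progression Criteria passes | Verdicts differ |
|---|---|---|---|---|
| 80% / 80% | 64% | 0.952 | 0.139 | 0.813 |
| 85% / 85% | 72% | 0.998 | 0.674 | 0.325 |
| 89.4% / 89.4% | 80% (as planned) | 1.000 | 0.981 | 0.019 |

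Every disagreement has the same direction: Table 1 passes and Progression Criteria fails.

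**The case against.** **The joint rule is the stronger one, so it simply binds.** A team that applies both sections gets a determinate answer, and Progression Criteria is the section that lists what is needed to advance. This has force, and it would be too strong to say that the decision cannot be evaluated. But Table 1 is also labelled as holding the progression thresholds, and nothing says which place governs or that both must be met.

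**The joint phrase may be shorthand for the two Table 1 rows.** Progression Criteria does not repeat its denominator, so this reading is possible. It fits poorly: retention is already listed there separately and would be counted twice, and the completer definition is joint.

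**The gap is a worst case.** Passing with about half of those enrolled needs both steps at their floors. The chat follows T0 immediately, and the US $45 payment covers the chat and T1, so heavy loss between them is not what the design expects. At the planned 80% the verdicts differ in about 2% of pilots. This stands as a limit on likelihood; the conflict matters when completion falls short of plan, which is when a progression rule is needed.

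**Stronger readings that the document does not support.** A reader might take the planned 80% (60 of 75) as a third version of the criterion. It is only the attrition projection behind the sample size, and a floor below the expected rate is ordinary. A reader might also object that nothing secures 60 completers, but no such rule is promised: the pilot is descriptive, and reach openly accepts 45 enrolled. Nor is the week-8 rule ("Prospective monitoring will trigger adaptive recruitment if fewer than 30 participants have been enrolled by week 8") an error for sitting below the on-pace 75 / 16 x 8 = 37.5. That is permissible slack. If enrollment is assumed Poisson with mean 37.5, a trigger of fewer than 38 would fire with probability about 0.51 when recruitment is exactly on plan, against about 0.09 for the existing one. Finally, the denominator sentence does not exempt reach, but Table 1 states reach against the target without ambiguity, so that is a minor clarification.

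**Conclusion.** The point holds as a conflict between two stated rules. Table 1 with its denominators accepts about 49% full completion among those enrolled (38 of 75, or 23 of 45); Progression Criteria requires 70% (53 of 75, or 32 of 45) and makes its own retention item redundant. The Table 1 retention threshold also does not match its measure.

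The conclusion rests on reading the joint criterion as a proportion of those enrolled, which the protocol's denominator rule supports. How often the conflict would bite depends on assumed stage rates: from about 2% of pilots at planned completion to 81% if each step runs at 80%.

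It needs correcting because it concerns a decision threshold. Its consequence is bounded: a missed criterion leads to a qualitative review of barriers and does not by itself end the program.

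**What to change.** Before phase 3 recruitment begins (projected for January 2027), state one completion rule, with its denominators, in both Table 1 and Progression Criteria. One workable form:

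- **Binding criterion:** full completers (pathway and T1) / enrolled of at least 70%.
- **Components, reported but not separately binding:** adoption = pathway completers / enrolled; retention = T1 completers / pathway completers.
- **Table 1 retention cell:** reword the threshold to T1 completion among pathway completers.

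If the sponsor prefers the two separate 70% floors, Progression Criteria should list adoption and retention in those terms, drop the joint item, and acknowledge that about 49% full completion would pass.

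Optionally, add to the denominator sentence that reach is judged against the target of 75.

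The cost is a table cell and a few sentences, with no change to sample size, data collection or the week-8 trigger. The downside of the joint rule is a stricter bar than Table 1 alone: 53 rather than 38 full completers at 75 enrolled.

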### Ethical Considerations

At the time of manuscript submission, all 3 phases of this study had been approved by the Institutional Review Board of the University of North Carolina at Chapel Hill (26-0669).

All participants will provide informed consent before any study activities begin. Individuals responding to social media recruitment will be directed to a Qualtrics screening link. For phase 1 interviews, eligible participants will be contacted by the research team via email restating the purpose of the study, with a link to self-schedule an interview conducted using an institutional Zoom (Zoom Video Communications) account. A trained member of the study team will confirm eligibility; describe the study’s purpose, procedures, risks, and benefits; and obtain verbal consent prior to the interview. For phase 2 feedback sessions and phase 3 chatbot interaction and surveys, consent will be obtained electronically via Qualtrics, where participants will review an information sheet detailing the study’s purpose, procedures, risks, and benefits and provide documented consent before any study activities begin. Data collection will follow a minimization approach: county and state of residence will be collected only to confirm rural eligibility, and each participant will be assigned a unique study ID. Identifiers (email address, county, and IP address) will be stored separately from research data and will never be merged with transcript or analytic files. Audio recordings will be transcribed and then permanently deleted following verification of transcript accuracy, and transcripts will be deidentified prior to analysis. Electronic data will be stored on secure, password-protected university servers with access restricted to authorized members of the research team, and SARHAchat back-end data will be stored on institutionally approved, secure AWS infrastructure with multifactor authentication.

Participants will access SARHAchat through a study URL and a unique study ID. Before engaging with the chatbot, participants must acknowledge a safety statement explaining that the chatbot provides informational support only and is not a substitute for clinical care and that they should consult a health care professional for evaluation, diagnosis, or treatment as needed (Figure 1). Participants will be instructed not to enter names, addresses, phone numbers, exact locations, names of partners or family members, or other directly identifying information into the chatbot. To further reduce unnecessary disclosure, phase 3 will offer 2 modes of engagement: guided prompts that allow participants to explore common SRH topics without typing personal questions and optional free-text entry for participants who wish to ask their own questions. High-risk prompts, including those involving urgent symptoms, sexual coercion, partner violence, or emotional crises, will trigger predefined safety and referral responses directing users to emergency, clinical, or crisis services as appropriate.

Participants will be compensated for their time in recognition of their contribution to the study. Compensation is structured by study phase: US $50 for phase 1 interviews, US $100 for phase 2 feedback session participation, and US $45 for phase 3 chatbot interaction and T1 survey completion, with an additional US $50 for those who choose to participate in a follow-up phase 3 interview.

## Results

The proposed research was funded in February 2026. Phase 1 semistructured interviews are scheduled to commence in May 2026; phase 2 community co-design sessions are planned for August 2026 to October 2026; and phase 3 pilot recruitment is projected to start in January 2027, with data collection concluding by October 2027. Full study results are anticipated to be submitted for publication in April 2028 (Table 2). At the time of protocol submission, a total of 14 participants have been enrolled in phase 1.

**Table 2. T2:** Projected timeline for proposed research activities and primary outputs.

Activity	Year 1 (2026)	Year 2 (2027)	Primary output
Protocol finalization and study launch	Quarter 1-quarter 2	—^a^	Approved protocol
Phase 1: semistructured interviews (target: n=24; range 14-32) and rapid thematic analysis	Quarter 2-quarter 3	—	Conceptual framework
Phase 2: co-design sessions and prototype revision	Quarter 3-quarter 4	—	Community-informed SARHAchat version 2
Phase 3a: pilot recruitment and data collection (16 wk) and pilot participant interviews (n=20)	—	Quarter 1-quarter 3	Feasibility dataset
Phase 3b: integrated analysis	—	Quarter 3-quarter 4	Feasibility manuscript

a Not applicable.

## Discussion

### Significance and Principal Contributions

This study represents a systematic effort to embed trust as a foundational design principle throughout the full development and community piloting cycle of an AI-enabled conversational health tool targeting rural young adults in the SRH domain. By generating a conceptual framework of rural trust determinants, producing community-derived design and implementation strategies, and piloting a social media–based deployment strategy, this research aims to inform responsible conversational AI design for this population and generate hypotheses that may transfer to other sensitive health domains and underserved communities.

The sequential design, moving from qualitative inquiry to participatory co-design to feasibility piloting, reflects a deliberate translational science logic grounded in implementation science. Each phase directly informs the next. This architecture seeks to avoid the common failure mode in AI health tool development in which tools designed without adequate community input generate poor engagement and this poor engagement is misattributed to community disinterest rather than design inadequacy [12,13,23].

### Innovation

This research reframes trust from a postdeployment outcome to a design input, operationalizing it as a multilevel construct with community-derived design requirements. To our knowledge, an explicit trust-by-design mapping of this kind has not been described in the SRH conversational AI literature, and the methods developed in this study may be adaptable to other sensitive health domains. The study also aims to demonstrate a community-informed process for developing conversational AI health tools that future research could draw on and adapt.

### Limitations

Phase 3 is not powered to detect the efficacy of SARHAchat; it is designed as a feasibility and signal detection study consistent with established recommendations for pilot work [27,39], and the findings will generate hypotheses about effectiveness. Recruitment via social media geofencing may introduce selection bias toward individuals with higher baseline digital literacy and existing social media access; the eHealth Literacy Scale administered at baseline will characterize this variability, and qualitative components will probe access as a barrier. The pilot does not measure long-term behavior change based on intervention use. Geographic restriction to NC and SC limits immediate generalizability, although the HRSA-based rural sampling strategy and emphasis on community-informed design principles are intended to maximize transferability within the rural US context.

### Future Directions and Impact

The primary contribution of this study is feasibility evidence: whether participants can be successfully recruited to and engage with a community-informed, trust-centered conversational agent and whether it can be sustained on the social media platforms that rural young adults already use. If the pilot meets progression criteria, the resulting feasibility estimates, refined implementation strategies, and exploratory signal detection data would inform the outcome selection and design for a subsequent effectiveness trial. Any criteria that are not met would indicate whether tool refinements or implementation strategy revisions are needed before an effectiveness trial is warranted. The phase 1 conceptual framework and the phase 2 and 3 community-informed methods aim to add to the emerging literature on responsible, equity-centered conversational AI design.

### Conclusions

This study describes a community-engaged research program designed to address a persistent equity gap in digital health: the limited treatment of trust as a design principle in AI-enabled health tools developed for rural and underserved communities. By generating a conceptual framework of trust determinants, a community-informed prototype, and feasibility data grounded in the lived experiences of rural young adults, this work aims to support more responsible development and implementation of conversational AI for communities facing persistent barriers to SRH care.
